## Background

Regular moderate intensity physical activity has been shown to positively influence the immune system [1,2]. Clinically this is represented by decreased incidence of upper respiratory tract infections (URTI) and pro-inflammatory markers in individuals who participate in regular moderate-intensity physical activity [2,3]. In contrast, most studies indicate that URTI rates increase during the 1-3 week period following marathon-type race events due to transient alterations in immunosurveillance [4-6]. Strenuous and prolonged exercise such as marathon running results in a major increase in inflammatory markers (e.g. C-reactive protein, interleukin 6) [6-8]. IL-6 is a cytokine with a wide range of biological effects, including pro-inflammatory influences during sepsis [9]. IL-6 is a central mediator of the acute-phase response and primary determinant of hepatic production of C-reactive protein (CRP) [10]. Elevated levels of IL-6 and CRP have been found in low-grade systemic inflammation such as atherosclerosis and diabetes mellitus [11,12]. In healthy men an elevated IL-6 plasma concentration has been associated with increased vascular risk and myocardial infarction [13]. IL-6 may stimulate blood coagulation and has been suggested to be an independent predictor for sudden death [14,15].

However, it is discussed equivocally whether IL-6 is primarily a pro- or anti-inflammatory cytokine. IL-6 activity appears to be essential for both the effective management of acute inflammation and to balance pro- and anti-inflammatory activity [16]. Post-exercise increases in plasma IL-6 are related to exercise workloads, with the highest levels found after strenuous and prolonged exercise [6-8]. Plasma IL-6 concentration decreases rapidly after strenuous exercise and is followed by increased levels of anti-inflammatory cytokines such as IL-1ra and IL-10 inducing an anti-inflammatory environment [2,17,18]. Chronic exercise, especially when accompanied with weight loss, is associated with decreased CRP and IL-6. This is linked to a reduced atherosclerosis and cardiovascular disease incidence [11,12].

Besides immune alterations, marathon running results in muscular damage which causes elevated levels of muscle enzymes (e.g. creatine kinase) and muscle soreness [19]. Additionally, changes of hemostasis leading to a pro-thrombotic state can be seen after a marathon race [20].

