### Sample size

Sample size calculation was based on the primary endpoint criterion, the difference in marathon-induced change of plasma IL-6 between the study groups. Due to the expected right-skewed distribution of IL-6, differences in changes of logarithmized IL-6 levels (relative group changes) were considered as the base for inferential statistics. From previous publications a coefficient of variation (CV) of 0.60 for IL-6 changes was expected for the proposed study population [45]. Assuming a true relative difference of at least 25% between the groups, a sample size of 80 individuals per group is necessary to detect a difference in IL-6 changes between both groups (given the CV of 0.60) with a power of 90% on a two-sided level of significance of 0.05.

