### Randomization

Participants will be randomized to Wobenzym or placebo in a 1:1 ratio using a pre-generated randomization list with variable block sizes.

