### Statistical methods

The difference of logarithmized IL-6 values will be calculated for each participant as distribution of IL-6 differences within the groups is expected to be skewed. Differences of logarithmized values will be compared between both study groups using a two-sample t-test. A two-sided level of significance of 5% will be considered for this primary efficacy analysis. Quantitative secondary endpoints will be analyzed using ANOVA methods, and qualitative data using chi-squared tests. Analysis of the primary endpoint and the secondary efficacy endpoints will be performed following the intention-to-treat (ITT) principle. These endpoints will also be assessed in the per-protocol dataset in the sense of sensitivity analyses.

The ITT dataset will consist of all trial subjects enrolled into the trial and randomized. For subjects with missing post marathon inflammation markers, a conservative replacement of the missing values will be conducted by imputing the lowest observed post marathon value for the placebo group and the highest observed value for the treatment group. The per-protocol dataset includes all trial subjects who were treated according to protocol. A tertiary dataset for analysis is the safety population. This population includes all trial subjects who received any IMP or other trial treatment.

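### Imputing opposite extremes for missing post-race IL-6 in the primary ITT analysis biases the estimate toward harm, so the two-sided 5% level and the 90% power fail once values are missing

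*Protocol article*

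**What the plan says.** All places are in the protocol article.

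- **Statistical methods, primary test.** Each man's difference in log IL-6 is compared between arms by a two-sample t-test. On the error level the section says: "A two-sided level of significance of 5% will be considered for this primary efficacy analysis".
- **Statistical methods, analysis sets.** The primary and secondary efficacy endpoints are analysed by intention to treat, in everyone enrolled and randomized. Where post-race inflammation markers are missing, the ITT set is completed by "imputing the lowest observed post marathon value for the placebo group and the highest observed value for the treatment group", a replacement the protocol describes as conservative. The per-protocol set serves for sensitivity analyses.
- **Sample size.** The calculation rests on two inputs: "Assuming a true relative difference of at least 25% between the groups", and "a coefficient of variation (CV) of 0.60 for IL-6 changes was expected for the proposed study population". It concludes that "a sample size of 80 individuals per group is necessary to detect a difference in IL-6 changes between both groups", the target being detection "with a power of 90% on a two-sided level of significance of 0.05".
- **Randomization.** Allocation is equal: "Participants will be randomized to Wobenzym or placebo in a 1:1 ratio".
- **Discontinuation.** Men who discontinue are not replaced.
- **Laboratory measurements and Background.** IL-10 is listed among the inflammation measures. The Background says that the post-exercise IL-6 surge is "followed by increased levels of anti-inflammatory cytokines such as IL-1ra and IL-10 inducing an anti-inflammatory environment".

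**The concern.** The rule is part of the primary analysis, not a stress test beside it. Each missing treatment value becomes the highest one seen and each missing placebo value the lowest, so both arms move against the product. The difference in means is therefore biased whenever anything is missing, even if loss is balanced and unrelated to outcome.

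With a two-sided test this has two consequences. A true 25% reduction can be missed, and an inert product can be declared significantly worse than placebo.

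Some missing values are foreseeable. Table 1 asks only for an intention to run the 2013 race, and recruitment precedes the race by weeks. A randomized man who does not start and gives no post-race sample stays in the ITT set. If he was allocated to treatment, he is given the highest post-marathon IL-6 observed, although he had no marathon stimulus.

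**Working it through.** **Inputs from the protocol:** two-sided alpha 0.05; power 90%; 25% relative difference; CV 0.60; 80 per arm; 1:1 allocation; t-test on log differences; the imputation rule.

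**Inputs assumed here:** number missing (equal in both arms, completely at random); normal log values; equal pre- and post-race SDs; pre-post correlation ρ of 0 to 0.6; extremes taken within each arm.

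**Step 1. Reproduce the sample size.**
- σ = √ln(1 + 0.60²) = √ln 1.36 = 0.5545
- δ = |ln 0.75| = 0.2877
- n = 2(1.960 + 1.282)² × 0.5545² / 0.2877² ≈ 78.1, so 79 per arm by the normal formula and 80 by the noncentral t. Power at 80 is 90.3%.

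The stated figure is reproduced, and it leaves no slack. Reading the effect as ln 1.25 would give 130 per arm, so a ratio of 0.75 is used below.

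**Step 2. Bias by hand.** The post-race SD is s = σ/√(2(1 − ρ)), which is 0.392, 0.469 and 0.620 for ρ = 0, 0.3 and 0.6. The largest or smallest of 70 to 80 normal values lies about 2.4 s from the mean. At ρ = 0.3 that is 2.4 × 0.4686 = 1.125 log units, or 1.125/0.5545 = 2.0 SDs of the log change that is tested. With m values missing per arm, the difference moves toward harm by about 2 × (m/80) × 2.4 s. At ρ = 0.3:
- m = 4: 2 × 0.05 × 1.125 = 0.112; −0.288 + 0.112 = −0.176; estimated ratio 0.84 instead of 0.75.
- m = 8: 2 × 0.10 × 1.125 = 0.225; −0.288 + 0.225 = −0.063; estimated ratio 0.94.

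**Step 3. Operating characteristics.** By simulation of the full rule and t-test, with thousands of trials per setting. The observed-values column is the noncentral-t power with 78, 76 or 72 men per arm.

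| Missing per arm | Power at ratio 0.75, ρ = 0 to 0.6 | Power, ρ = 0.3 | Significant harm, inert product, ρ = 0 to 0.6 | Power, observed values only |
|---|---|---|---|---|
| 0 | 90% | 90% | 2.5% | 90.3% |
| 1 (1.25%) | 84% to 78% | 82% | not tabulated | not tabulated |
| 2 (2.5%) | 76% to 60% | 71% | not tabulated | 89.6% |
| 4 (5%) | 55% to 26% | 45% | 16% to 29% | 88.8% |
| 8 (10%) | 17% to 1% | 8% | 50% to 77% | 87.1% |

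In the other direction, false claims of benefit for an inert product fall from about 2.5% to below 0.1% at 5% missing.

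**Step 4. A different baseline model.** Let the log change (SD 0.5545) be independent of baseline, with baseline log SD 0, 0.3 or 0.6. The post-race SD is then larger and so is the damage. Power is 34%, 26% and 10% at 5% missing, and false harm is 73%, 80% and 91% at 10%. The protocol's sentence also permits extremes taken over both arms; in this model that lowers power at 5% missing to 17%, 10% and 3%.

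**The case against.** **The loss is conditional.** A reader might infer that the rule removes most of the power outright. The documents do not support that. They give no missing rate, and with complete data the rule does nothing. With 1 or 2 values missing per arm, 60-84% power remains in the main model. At 5% the loss runs from about 35 to 64 points; only near 10% is most of the power gone in every setting tried. The exact figures depend on a post-race SD that the protocol does not give. This objection stands, and it sets how the point is worded.

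**The rule is conservative for the hypothesis of interest.** This also stands: a false claim of benefit becomes very unlikely. It does not rescue a test declared two-sided, because the error moves to the other tail and grows.

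**A per-protocol analysis is prespecified.** True, and readers would have a second result. But it is a sensitivity analysis and does not repair the primary one.

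**IL-10.** A reader might infer that giving treated men the highest IL-10 favours the product. The protocol names no favourable direction for IL-10, and the Background describes its rise as following the IL-6 surge, so a product that dampens inflammation might lower it. What stands is narrower: for IL-10 the rule cannot be assumed to be conservative.

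**Other methods also give non-starters a value.** Correct. A missing-at-random method implicitly assigns them a marathon response, so their handling has to be stated.

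**The article allows nothing for attrition.** In a condensed article that is not a fault in itself, and no separate point is made of it.

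**Conclusion.** The point holds in conditional form. The rule is stated in the protocol and belongs to the primary analysis, so a separate analysis plan could not undo it without departing from the protocol. Whenever a post-race value is missing, the IL-6 estimate is biased toward harm, and the two-sided 5% level and the 90% power no longer apply as stated.

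If 5% are missing per arm, power at the design effect is roughly a quarter to a half, and an inert product looks significantly harmful in about one trial in six to more than one in four. If 10% are missing, power is 17% or less and false harm occurs in at least half of trials. These sizes rest on the assumed missing rate, correlation, normality and random missingness. The direction of the bias depends on none of these magnitudes when loss is random. Since observed values alone keep about 89% and 87% power, the rule and not the lost data does the damage.

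**What to change.** Before unblinding, amend the protocol and analysis plan as follows.

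1. Base the primary ITT analysis on a missing-at-random method: a likelihood-based mixed model on all ln IL-6 values, or multiple imputation using arm and the visit 1 and visit 2 ln IL-6 values.
2. State how randomized men who do not start the race enter the primary analysis.
3. Keep the opposing-extremes rule only as a labelled sensitivity analysis for IL-6, or replace it with a delta-adjusted tipping-point analysis. If it stays, say whether extremes are taken within an arm or over both.
4. Do not apply it to IL-10 or the other secondary markers.

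The cost is wording and a little programming, with no extra participants or data. The downside is reliance on the missing-at-random assumption, which the sensitivity analysis tests. The 89% and 87% figures are for observed values; power for the chosen method should be confirmed once it is specified.

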### Data management

The trial database will be based on the MARVIN system, an electronic data base developed for clinical trials. The system is CDISC certified, well defined and represents a worldwide accepted data and documentation standard. This approach allows online plausibility checks and automated queries, and contains automatic validation rules. Every modification will be automatically tracked during the trial.The database is integrated in an IT infrastructure and safety system containing a backup and firewall system. The data are saved on a daily basis.The medical data in this trial are to be recorded in eCRFs. After completing the data input (including data cleaning) the database will be locked and can be exported for statistical analysis in SPSS or SAS format.

## Discussion

The Enzy-MagIC trial will investigate the effects of oral hydrolytic enzymes and flavonoids (Wobenzym) on marathon-induced changes in inflammation, muscle impairment, and rheological status in healthy males. Previous studies indicate that Wobenzym has anti-edematous, anti-inflammatory, antioxidant, and fibrinolytic effects [34,39,40]. Thus the hypothesis for this study is that Wobenzym supplementation for one week before and two weeks after participation in a competitive marathon race will mitigate inflammation and muscle damage, lower URTI incidence, and attenuate pro-thrombotic hemostatic changes.

Plasma IL-6 concentration is increased after strenuous prolonged exercise such as marathon running [6-9]. Polyphenols and trypsin may decrease IL-6 release [29,46,47] whereas bromelain may alter the release of other pro-inflammatory factors [35]. Thus a primary objective of this study is to investigate the effect of a mixture of rutoside, trypsin, and bromelain on marathon-induced changes in plasma IL-6. If proven to be efficacious in this setting, Wobenzym may emerge as a suitable alternative to NSAIDs.

Supplementation of a mixture of flavonoids has been reported to have anti-inflammatory and antioxidant effects after exercise [27,28]. Results from a randomized double-blind study with human marathon athletes ingesting a polyphenol-rich beverage for 3 weeks before and 2 weeks after marathon race showed a reduced incidence of URTI [6]. The athletes in this study drank 1-1.5 liters of non-alcoholic beer per day, making this approach very challenging. The use of Wobenzym tablets containing hydrolytic enzymes and flavonoids simplifies the supplementation process and should improve compliance.

Supplementation with bromelain in children with sinusitis showed a significantly faster recovery from symptoms compared to standard therapy [33]. Therefore the use of supplements with a mixture of hydrolytic enzymes and flavonoids might be a promising approach to attenuate marathon-induced immune dysfunction and lower URTI incidence and symptom severity.

Marathon running induces significant muscle soreness and damage, with large increases in creatine kinase and myoglobin [19]. Muscular damage and glycogen depletion have been associated in other studies with post-exercise increases in IL-6 and other inflammatory parameters [7]. Therefore, attenuation of muscle soreness and damage through use of Wobenzym should result in lower post-race plasma levels of IL-6. Other studies indicate that following injury, Wobenzym decreases pain and swelling, and is as effective as the nonsteroidal anti-inflammatory drug diclofenac [34,48].

Following marathon race participation, athletes experience changes of hemostasis associated with a pro-thrombotic state [20]. Two studies investigated the effect of bromelain on platelet aggregation. In vitro bromelain proteases reduced human platelet aggregation [49]. In rats Livio et al. also demonstrated reduced platelet aggregation and fibrinolytic effects after administration of bromelain [50]. Orally applied bromelain showed an inhibition of thrombus formation in rat mesenteric vessels [49].

In summary, ingestion of oral hydrolytic enzymes and flavonoids is hypothesized to function as a countermeasure strategy to marathon-induced inflammation, muscle damage and soreness, negative changes in rheological status, and increased URTI incidence. These negative physiologic effects after marathon competition prolong recovery. For athletes it is very important that the regeneration is as effective and as short as possible. A product that could support recovery from strenuous exercise would be beneficial not only for high-performance athletes but also for non-elite athletes.

## Abbreviations

ANOVA: Analysis of variance; CDISC: Clinical data interchange standards consortium; CK: Creatine kinase; (hs-)CRP: (high-sensitivity) c-reactive protein; eCRF: Electronic case report form; GCP: Good clinical practice; GOT: Glutamate oxalacetate transaminase; IL: Interleukine; IMP: Investigational medical product; LDH: Lactate dehydrogenase; SPSS: Statistic package for social sciences, statistical program; SAS: Statistical data format; SAE: Serious adverse event; tPA: Tissue plasminogen activator; URTI: Upper respiratory tract infections.
